##### Randomization and Blinding

Following consent, participants will be randomized into either an intervention arm that comprises usual clinical care plus access and use of the digital resources or a control arm comprising usual clinical care and access to nondementia resources (eg, a pamphlet on healthy living). Randomization will be done using computer-generated random number sequences, and the process will be overseen by a researcher not involved in the study. After allocation to groups, participants will be able to choose to receive specific instructions on how to access materials relevant to the condition (a brief instructional booklet) they have been allocated to either electronically, by regular mail, or in person. As a booster, participants in the intervention arm will also receive a monthly phone call from the research associate to help sustain intervention engagement over the long term, which is a risk to any digital trial [25]. Caregivers will not be told whether they are in the intervention or the control group to reduce potential bias. However, this blinding is not expected to be of any disadvantage, as all participants will have free and unlimited access to the Moving Pictures India materials after the pilot RCT.

##### Outcome Measures

The primary outcome measures for the pilot RCT will be feasibility and acceptability, while the secondary outcome measures for the pilot RCT will be (1) caregiver burden, as measured by the Zarit Burden Interview [26]; (2) caregiver mood, as measured by the Center for Epidemiological Studies Depression 10-item scale [27]; and (3) caregiver quality of life, as measured by the World Health Organization Quality of Life Scale [28].

Validated, translated versions of the Zarit Burden Interview and World Health Organization Quality of Life Scale measures are already available in English, Hindi, and several other Indian languages. All the secondary outcome measures will be self-rated and measured at baseline, 3 months, and 6 months via regular mail, telephone, or online. Sociodemographic data (eg, age, gender, socioeconomic status, relation to the person with dementia, years as a caregiver) will also be collected. The schedule of enrolment, interventions, and assessments for the pilot RCT is presented in Figure 3.

**Figure 3 figure3:**
[figure not shown]
SPIRIT (Standard Protocol Items: Recommendations for Interventional Trials) flowchart of the schedule of enrollment, interventions, and assessments for the phase 3 pilot randomized controlled trial.

##### Statistical Analysis

To estimate parameters of feasibility and acceptability with sufficient precision, which will help inform the future implementation trial, 40 participants from the intervention arm and 20 from the control arm are expected. The expected values for the proportion of family caregivers rating the intervention as “very acceptable” are 70% (95% CI 59%-87%) or 70% (95% CI 62%-85%) for participants for whom outcomes are completed at the 6-month follow-up. Achieving these expected values will be a priori criteria for progression to an implementation trial without modification of the intervention.

Repeat measures ANOVA will examine changes over time. The proportions of eligible family caregivers approached who agreed to take part in the study will be reported with a 95% CI, and any reasons for refusal will be summarized. Characteristics of people with dementia and their family caregivers that are included in the study will be summarized using means (with SD), medians (with interquartile ranges), counts, and proportions, as appropriate. Scores measured pre- and postintervention will be summarized at each time point (eg, using means and SD) and as differences between the randomization groups with 95% CI. Completeness of these scores will also be described. We will estimate parameters to help inform development of the implementation trial, particularly, the proportion of family caregivers using the intervention and for whom outcomes were completed at the 6-month follow-up.

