#### Phase 3. Pilot RCT: Intervention Assessment

To evaluate the impact of the resources produced, a pilot RCT will be conducted in the second and third year of the study (Figure 2). The pilot RCT will follow an experimental parallel group design with two arms aiming to assess the impact, feasibility, and acceptability of the resources of Moving Pictures India. The aims of the pilot RCT will be: (1) to test the feasibility of a full RCT with feasibility prespecified as >70% of participants expressing interest, consenting to participate, and >80% participation in follow up; (2) to test acceptability, prespecified as >70% of participants rating the intervention “very acceptable.”

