## Results

This study was funded by the Alzheimer’s Association. It brings together complementary expertise across multiple disciplines such as anthropology, psychology, psychiatry, geriatrics, film and media studies, disability studies, and social work.

Postdissemination analytics and qualitative feedback will be used to develop an implementation trial; explore how different strategies for dissemination and integrating the resources in local service provisions impact relevant caregiver variables like caregiver burden, mood, and quality of life; and evaluate the effects of the approaches to improve the uptake and utilization of the intervention. From July to December 2023, we will enroll 60 dementia caregivers (40 caregivers in the intervention group and 20 in the control) for the pilot RCT and follow them up for 6 months. This study is expected to conclude in June 2024.

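### Neither 95% CI printed beside the expected 70% belongs to 70% at n=40 or n=60, so the proportion, parameter and denominator behind the sample size and progression criterion are unclear

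*Protocol article*

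**What the plan says.** All places are in the protocol article, Methods, Phase 3, unless stated.

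- **Basis of the sample size (Statistical Analysis).** The stated aim is "To estimate parameters of feasibility and acceptability with sufficient precision", and for this "40 participants from the intervention arm and 20 from the control arm are expected". The Results section repeats the total: "we will enroll 60 dementia caregivers (40 caregivers in the intervention group and 20 in the control".
- **Expected values (same paragraph).** The proportions rating the intervention very acceptable "are 70% (95% CI 59%-87%) or 70% (95% CI 62%-85%) for participants for whom outcomes are completed at the 6-month follow-up". No CI method is named and neither interval has a denominator.
- **Use of the figures (same paragraph).** "Achieving these expected values will be a priori criteria for progression to an implementation trial without modification of the intervention".
- **Thresholds (opening paragraph of Phase 3).** Acceptability is ">70% of participants rating the intervention “very acceptable". Feasibility includes ">80% participation in follow up".
- **Who can rate the films (Randomization and Blinding).** Only the intervention arm has the digital resources during the trial. Controls receive material unrelated to dementia and get the films afterwards.

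**The concern.** A 95% CI around 70% should be centred on 70% (Wald) or a little below it (exact, Wilson, Agresti-Coull, Jeffreys). The printed intervals are centred on 73% and 73.5%. The second is said to describe participants with completed 6-month outcomes, apparently a subset, yet it is narrower than the first: 23 points wide against 28.

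In this article these figures are the only support for the claim of sufficient precision, acceptability is a primary outcome, and the next sentence turns the same figures into the progression criterion. If the proportion and its limits disagree, a reader cannot tell whether 70% or 75% was intended, or what the second interval measures.

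**Working it through.** **Inputs.** Expected proportion 70%; printed limits 59%-87% and 62%-85%; 40 intervention and 20 control, total 60 (Statistical Analysis; Results). Follow-up criterion >80% (opening of Phase 3). Two-sided 95% limits are assumed, since both limits are printed.

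**Formulas**, with x raters out of n, p = x/n, z = 1.96:

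- Wald: p ± z√(p(1−p)/n)
- Wilson: [x + z²/2 ± z√(x(n−x)/n + z²/4)] / (n + z²)
- Exact (Clopper-Pearson): lower = 2.5% quantile of Beta(x, n−x+1); upper = 97.5% quantile of Beta(x+1, n−x)

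**Step 1: try to reproduce the printed limits at 70%.** Wald at n=40: 0.70 ± 1.96√(0.21/40) = 0.70 ± 0.142. Wald at n=60: 0.70 ± 1.96√(0.21/60) = 0.70 ± 0.116.

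| x/n | p | Wald | Wilson | Exact |
|---|---|---|---|---|
| 28/40 | 70% | 55.8-84.2 | 54.6-81.9 | 53.5-83.4 |
| 42/60 | 70% | 58.4-81.6 | 57.5-80.1 | 56.8-81.2 |
| 30/40 | 75% | 61.6-88.4 | 59.8-85.8 | **58.8-87.3** |
| 45/60 | 75% | 64.0-86.0 | 62.8-84.2 | **62.1-85.3** |

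Agresti-Coull and Jeffreys at 28/40 give 54.5-82.0 and 54.8-82.4. Neither printed interval is reproduced at 70%. Rounding cannot explain this: rounding each limit to a whole per cent moves the midpoint by at most 0.5 points, and the printed midpoints are (59+87)/2 = 73 and (62+85)/2 = 73.5.

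**Step 2: find what does produce them.** Every x/n with n from 15 to 100 was searched under these five methods and continuity-corrected Wald and Wilson. All matches have p between about 73% and 76%; none has 70%.

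- 59-87: the exact method matches only 30/40. Other methods match at other denominators, for example 27/37 (Wald), 25/33 (Wilson) and 27/36 (Jeffreys).
- 62-85: the exact method matches 45/60, 44/59 and 47/63. Wald also matches 44/60 = 73.3%. The smallest n under any method is 49 (37/49, Wilson).

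The exact method at 75% reproduces both intervals at the trial's own denominators, 40 and 60.

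**Step 3: separate width from position.**

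| | Printed half-width | At 70%: Wald / Wilson / exact | Printed lower limit minus lower limit at 70% |
|---|---|---|---|
| First, n=40 | 14.0 | 14.2 / 13.7 / 15.0 | 59 − 55.8 = 3.2 to 59 − 53.5 = 5.5 |
| Second, n=60 | 11.5 | 11.6 / 11.3 / 12.2 | 62 − 58.4 = 3.6 to 62 − 56.8 = 5.2 |

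The widths are nearly right; the limits are shifted upward.

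**Step 4: the second interval under its two readings.**

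- *Acceptability among completers, as the sentence literally says.* Raters number at most 40, and 62-85 needs at least 49, so it cannot arise. With 32 completers (0.80 × 40, the boundary of the follow-up criterion, used as an illustration), exact limits are 50.0-83.9 for 22/32, 53.3-86.3 for 23/32 and 56.6-88.5 for 24/32.
- *6-month completion among all 60.* Then n=60 is legitimate, but 70% (42/60) still gives 56.8-81.2. More than 80% of 60 needs at least 49 completers (48/60 is exactly 80%), while 70% is 42 and 75% is 45. The expected value would miss the trial's own feasibility criterion.

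**Step 5: effect on the progression rule at n=40.** 28/40 = 70% achieves an expected value of 70% but is not >70%. 29/40 = 72.5% passes both of those but fails at 75%. 30/40 passes all three.

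**The case against.** The strongest reply has three parts.

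1. *Precision is about width, and the widths are fine.* This stands. Both printed half-widths are within about one point of those for 70% at n=40 and n=60. A reader might infer that the trial is less precise than claimed and needs more participants; the figures do not support that.
2. *The second interval may not concern acceptability.* The sample-size sentence covers feasibility as well as acceptability and counts both arms. The end of the same section also lists use of the intervention with complete 6-month outcomes as something to estimate. A reader might infer that 20 controls were counted as rating films they never saw, or that the second interval is impossibly narrow on any reading. Neither is established: on the completion reading n=60 is proper and a narrower interval is expected. That reading still does not rescue the 70% or the sentence's wording, and it creates the conflict with the follow-up criterion.
3. *The rule is a point threshold, so a misplaced lower limit changes no decision.* This stands in part. The article sets no rule on a lower confidence limit. But the progression sentence refers back to these expected values, and if 75% was intended, 29/40 would be judged differently.

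A reader might also take 75% as the documented plan. It is a strong inference from the numerical match, but the article never gives that figure or names a CI method.

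**Conclusion.** The point holds as an error of labelling and position. Neither printed interval belongs to 70% at n=40 or n=60 under any standard method. Both are consistent with exact limits for 75% at 30/40 and 45/60. The limits are about 3 to 5.5 points too high at the lower end; for acceptability among 40 at 70%, the lower limit is about 53.5%-56% rather than 59%. The second interval is unattainable on the literal reading. On the completion reading it is mislabelled and at odds with the >80% criterion.

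This rests on two-sided 95% limits and on raters being confined to the 40 intervention participants. The 32-completer figures apply only if the second interval means acceptability among completers. The full protocol is not at hand, so the statement that these figures are the only sample-size justification applies to the article alone.

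**What to change.** Rewrite the expected-values sentence so that each interval carries its parameter, expected proportion, denominator and CI method, with matching limits.

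- **Acceptability, intervention arm, n=40:** either 70% (28/40), exact 95% CI 53%-83%, or 75% (30/40), exact 95% CI 59%-87%.
- **Second interval, if acceptability among completers:** use the expected number of intervention-arm completers. With 32, for example, exact limits are 50%-84% (22/32), 53%-86% (23/32) or 57%-89% (24/32).
- **Second interval, if 6-month completion:** label it so, keep n=60, and reconcile the expected value with the >80% follow-up criterion.

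Then state which value is the progression criterion, whether it must be reached or exceeded, and make it agree with the >70% rule at the start of Phase 3.

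The cost is wording only. No participants are added. If 70% is kept, the printed limits move down; if 75% is adopted, the first interval stands and the expected proportion changes.

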### Limitations

Although there are no foreseeable risks associated with participation in this study, there are some factors that may hinder recruitment and participant retention. Digital media is not a common support intervention for caregivers of persons with dementia in India, and acceptance of the program, especially by older caregivers such as spouses, could hamper recruitment. Lack of time to take part in the study due to care responsibilities could also be a factor in retention and recruitment. Nonadherence in eHealth interventions has been reported to be high in earlier studies [37,38]. Another limitation could be that only motivated and active caregivers who are internet or media savvy will take part in the study, which could possibly limit the generalizability of the results and acceptance of the program for the anticipated larger trial. Notwithstanding the limitations, the protocol includes potentially useful approaches for implementation, the most significant of which is the involvement of stakeholders and the utilization of a multifaceted approach involving a mixture of interactive workshops, feedback, reminders, and local consensus processes in the design of the research to ensure relevance [39,40].

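### The acceptability criterion for progression is stated with two denominators, one of them 6-month completers only, and the plan does not say which decides

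*Protocol article*

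**What the plan says.** The Phase 3 introduction of the protocol article defines acceptability as ">70% of participants rating the intervention" 'very acceptable', with no mention of completers. It also sets a separate feasibility criterion of ">80% participation in follow up", without saying whether this applies per arm or overall.

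The Statistical Analysis section says "40 participants from the intervention arm and 20 from the control arm are expected". It gives the expected acceptability as "70% (95% CI 59%-87%) or 70% (95% CI 62%-85"%), and attaches to the second figure the words "for participants for whom outcomes are completed at the 6-month follow-up". The rule follows: "Achieving these expected values will be a priori criteria for progression to an implementation trial without modification of the intervention". That section does not say whether one version or both must be reached, or how a caregiver with no rating is counted. Under Outcome Measures, acceptability is a primary outcome.

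**The concern.** A go criterion needs one population. Here the aims point to participants, while the analysis section offers a second version that, read literally, removes anyone without 6-month outcomes. If caregivers who dislike the films are more likely to be lost, removing them raises the proportion, and dropout then helps to meet the acceptability criterion. At stake is a primary outcome of the pilot and the decision to go to an implementation trial with the intervention unchanged.

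**Working it through.** **Inputs.** 40 caregivers allocated to the intervention and 20 to control (Statistical Analysis); acceptability above 70% and follow-up above 80% (Phase 3 introduction). No dropout rate is given, so the number of completers is varied below.

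**The plan's own intervals.** The Wald interval is p ± 1.96 × √(p(1 − p)/n).
- n = 40: 0.70 ± 1.96 × √(0.21/40) = 0.70 ± 0.142, or 55.8% to 84.2%. The exact (Clopper-Pearson) interval is 53.5% to 83.4%.
- n = 60: 0.70 ± 1.96 × √(0.21/60) = 0.70 ± 0.116, or 58.4% to 81.6%. The exact interval is 56.8% to 81.2%.

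Neither gives 59%-87% or 62%-85%. A search over every count with n from 10 to 119, using five interval methods (Wald, Wilson, Agresti-Coull, exact, Jeffreys), found:
- 59%-87% only for n from 33 to 40, including the exact interval for 30/40 = 75%;
- 62%-85% only for n from 49 to 63, including the exact interval for 45/60 = 75%.

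A subset of the 40 should have a wider interval than the full 40. The second interval is narrower and fits the whole trial of 60. Its wording says completers, but its width does not.

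**Effect of the denominator.** With c completers, the smallest count above 70% is r = floor(0.70c) + 1. If every non-completer is counted as not 'very acceptable', the share of those allocated is r/40.

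| Completers c | Needed r | r/c | r/40 |
|---|---|---|---|
| 40 | 29 | 72.5% | 72.5% |
| 34 | 24 | 70.6% | 60.0% |
| 33 | 24 | 72.7% | 60.0% |
| 32 | 23 | 71.9% | 57.5% |
| 29 | 21 | 72.4% | 52.5% |
| 28 | 20 | 71.4% | 50.0% |

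**Limit set by the retention criterion.**
- Within the arm: above 80% of 40 means at least 33 (82.5%). The floor is 24/40 = 60%.
- Overall: above 80% of 60 means at least 49. With all 20 controls retained, 49 − 20 = 29 intervention completers suffice. The floor is 21/40 = 52.5%.
- With 28 completers, overall follow-up is at most (28 + 20)/60 = 80%, which is not above 80%.

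**How far the worst case matters.** At 33 completers with 24 positive, 7 caregivers have no rating. Passing on all 40 needs 29, so 29 − 24 = 5 of those 7 would have to be positive. At 29 completers with 21 positive, it would take 29 − 21 = 8 of 11. With any fewer, the two denominators give opposite decisions.

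**The case against.** The strongest objection is that there may be no completer-only acceptability estimate at all. The second interval fits n = 60, and the last sentence of Statistical Analysis lists completion of 6-month outcomes as a parameter of its own. The text may have run together acceptability in 40 and follow-up completion in 60. This is plausible, but it does not rescue the criterion. Under Randomization and Blinding, control caregivers get non-dementia resources during the trial, so 60 is not a sensible base for rating the films, and the rule as printed would still be misstated.

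A reader might infer three stronger things that the documents do not support.
- *That the sponsor may choose the favourable version.* The progression sentence is in the plural and can be read as requiring both values; the 'or' stands in the sentence before it. What stands is that the text leaves this open.
- *That progression is possible with only 50% of those allocated positive.* That needs 28 completers, which misses the follow-up criterion on either reading. The progression sentence does not repeat that criterion, but the abstract's Conclusions make the next trial conditional on the intervention being both feasible and acceptable. Dropout therefore also counts against progression through feasibility.
- *That upward bias is shown, or that the protocol predicts heavy dropout.* The Limitations section says only that "Nonadherence in eHealth interventions has been reported to be high in earlier studies". It also names lack of time because of care duties as a reason for poor retention, and not using the films differs from not returning outcomes. Bias is plausible, not demonstrated.

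It can also be said that missing-data handling belongs in an analysis plan that is not shown, and that counting missing ratings as negative penalises dropout twice. The first point does not cover a rule that the article itself states, calls a priori and gives with conflicting denominators. The second is a fair cost of the remedy.

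**Conclusion.** The point holds as a defect in a stated decision rule. The acceptability criterion has two versions, the second literally limited to 6-month completers and at odds with the Phase 3 definition, and nothing says which governs. The completer version can pass when the allocated version fails: 72.7% against 60% with retention met within the arm, and down to 52.5% of those allocated if retention is judged overall and every loss falls in the intervention arm. These figures are illustrative. They rest on assumed numbers of completers and on the worst case that non-completers would not rate the films 'very acceptable'. The mismatch between the second interval and its described population is a further sign that the sentence needs rewriting. The criterion should be corrected before the go decision; the design itself is unaffected.

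**What to change.** State one decision denominator, consistent with the Phase 3 aims: all caregivers randomised to the intervention arm (40), with a missing rating counted as not 'very acceptable' for the go decision. Report the completer proportion as a sensitivity estimate only. Use an earlier rating in place of a missing one only if acceptability is actually collected at that visit; Outcome Measures schedules 3-month assessment for the secondary outcomes only. If the second figure was meant as follow-up completion in all 60, give it separately under that name, and make each point estimate agree with its interval.

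The change is to wording and needs no extra participants. Its cost is a more conservative primary figure: 29 of 40 positive ratings are needed whatever the dropout, so with 33 completers 29/33 = 87.9% of them must be positive, and with 29 completers all of them. Because dropout then counts under both acceptability and feasibility, the completer estimate should be shown beside the decision figure.

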**Conclusions:**

This protocol is designed to deliver unique, coproduced, and evidence-based media resources to support caregivers of persons with dementia in India and other countries aiming to utilize digital media for dementia care. If the intervention is found feasible and acceptable, postpiloting analytics and qualitative feedback will be used to develop an implementation trial to evaluate the effectiveness of the potential low-risk high-benefit intervention in practice.

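### The criterion for progressing without modification is stated inconsistently: more than 70% versus achieving 70%, no link to the feasibility thresholds, and an expected value whose intervals belong to 75%

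*Protocol article*

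**What the plan says.** Four places in the protocol article bear on the decision after the pilot.

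- **Phase 3. Pilot RCT: Intervention Assessment (aims).** Aim 1 has "feasibility prespecified as >70% of participants expressing interest, consenting to participate, and >80% participation in follow up". Aim 2 is "to test acceptability, prespecified as >70% of participants rating the intervention" as *very acceptable*. Both use a strict inequality.
- **Statistical Analysis, planning values.** The section states that "40 participants from the intervention arm and 20 from the control arm are expected". The expected proportions rating the intervention *very acceptable* "are 70% (95% CI 59%-87%) or 70% (95% CI 62%-85%) for participants for whom outcomes are completed at the 6-month follow-up".
- **Statistical Analysis, progression.** The next sentence reads: "Achieving these expected values will be a priori criteria for progression to an implementation trial without modification of the intervention". Consent is then to be reported with a 95% CI. Among the quantities to be estimated is "the proportion of family caregivers using the intervention and for whom outcomes were completed at the 6-month follow-up". Neither is given a threshold in this section.
- **Abstract, Conclusions.** The next step is conditional in general terms: "If the intervention is found feasible and acceptable, postpiloting analytics and qualitative feedback will be used to develop an implementation trial".

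Outcome Measures names feasibility and acceptability as the primary outcomes. Postpilot Revision allows changes to the intervention after the pilot.

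**The concern.** Feasibility and acceptability are the primary outcomes, and the progression sentence turns them into a decision. Four features leave that decision open to more than one reading.

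1. The aims need more than 70%, while the analysis section needs 70% to be achieved. A result of exactly 70% is a pass in one place and a fail in the other.
2. The only sentence labelled as progression criteria attaches to the *very acceptable* proportions. It does not name the consent or follow-up thresholds, although the Abstract makes the next trial depend on feasibility as well.
3. The second 70% can be read as acceptability among 6-month completers or as a completion target. The two readings give different rules.
4. The printed intervals do not fit 70%, so the expected values that must be achieved are themselves uncertain.

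A rule with several readings can be settled after the data are in, which defeats the purpose of fixing it beforehand.

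**Working it through.** **Inputs.** From Statistical Analysis: 40 intervention and 20 control participants (60 in all), expected values of 70%, and intervals 59%-87% and 62%-85%. From the Phase 3 aims: more than 70% for acceptability and consent, more than 80% for follow-up. The number who will give a rating is not stated. I assume all 40 unless noted.

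**Step 1: the printed intervals.** The exact (Clopper-Pearson) 95% limits for x out of n are the 2.5% quantile of Beta(x, n-x+1) and the 97.5% quantile of Beta(x+1, n-x).

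| x/n | Proportion | Exact 95% CI | Printed |
|---|---|---|---|
| 28/40 | 70% | 53.5%-83.4% | none |
| 42/60 | 70% | 56.8%-81.2% | none |
| 30/40 | 75% | 58.8%-87.3% | 59%-87% |
| 45/60 | 75% | 62.1%-85.3% | 62%-85% |

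At 70%, the Wald (55.8%-84.2%) and Wilson (54.6%-81.9%) intervals for n = 40 do not match either. The printed figures are therefore not reproduced at 70%. At 75% the exact method gives both, with n = 40 and n = 60.

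**Step 2: what the second value could be.** Completers in the intervention arm number at most 40, so at the same proportion their interval cannot be narrower than that of the full 40. The second printed interval is narrower (85 - 62 = 23 points against 87 - 59 = 28 points) and fits all 60 participants. It may therefore be a completion proportion over both arms, although the sentence literally describes acceptability among completers.

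**Step 3: the conflict at the threshold.** 0.70 × 40 = 28. Achieving 70% needs X ≥ 28 and exceeding 70% needs X ≥ 29. With X ~ Binomial(40, p):

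| True rate p | P(X ≥ 28) | P(X ≥ 29) | P(X = 28), rules disagree |
|---|---|---|---|
| 60% | 0.129 | 0.071 | 0.058 |
| 70% | 0.577 | 0.441 | 0.137 |
| 75% | 0.821 | 0.715 | 0.106 |
| 80% | 0.957 | 0.912 | 0.044 |

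The conflict needs 0.70 × n to be a whole number, so n must be a multiple of 10. With 36 raters both rules need 26, and with 32 both need 23.

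If 75% was the value meant, achieving it needs X ≥ 30. At a true 70% that has probability 0.309.

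**Step 4: leaving follow-up out.** Read literally, if 20 of 40 complete (50%), then 14/20 = 70% meets the completer criterion. Follow-up is far below 80%, and only 14/40 = 35% of those randomised to the intervention gave the rating.

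More generally, more than 80% of 60 is at least 49 (0.80 × 60 = 48). With true acceptability 80% and true retention 75%, P(X ≥ 29 of 40) = 0.912 and P(at least 49 of 60 retained) = 0.148. Acceptability alone passes 0.91 of the time. Requiring both gives 0.912 × 0.148 ≈ 0.13, assuming independence and all 40 rated.

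**The case against.** The strongest reply is that this is a wording matter in a condensed report of a pilot.

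- **Scope of the criterion.** It governs only progression without modification, and Postpilot Revision provides for changes. A reader might infer that missing 70% ends the programme. No passage says so. This stands.
- **Feasibility is not absent.** The aims prespecify it, Outcome Measures makes it primary, and the Abstract says "If the intervention is found feasible and acceptable". A reader might infer that the plan disregards failed retention. That follows only if the progression sentence is read alone. This stands; what remains is that the progression sentence does not refer back to the thresholds.
- **Retention may be in the rule.** If the second value is a completion target, retention is included. But it is then set at 70%, against more than 80% in the aims, so one inconsistency replaces another.
- **Pass probability near one half.** A reader might infer from 44% and 58% at a true 70% that the decision is close to chance. Any cut-off behaves this way when the truth lies on it. The rule separates 60% (7% to 13%) from 80% (91% to 96%), and if 75% was the planning value the figures are 72% to 82%. This stands.
- **The conflict is one participant wide**, and it disappears for most numbers of raters below 40. This limits its size, but 40 is the protocol's own figure.

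**Conclusion.** The point holds as an inconsistency in a prespecified criterion, and it should be fixed. At 28/40 the two sections give opposite answers, with probability 13.7% at a true 70% and 10.6% at 75%, assuming all 40 rate. The progression sentence omits the consent and follow-up thresholds, so a pilot that fails follow-up can meet it. The second 70% has two readings: on the literal one the sentence sets no completion threshold, and on the other it contradicts the aims. Both printed intervals are exact intervals for 75%, so it is unclear whether the expected value is 70% or 75%. That 75% was intended is an inference from the match; the document does not say it.

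The documents do not support saying that the rule decides whether the programme continues at all, that it works by chance, or that feasibility plays no part.

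**What to change.** State one rule, in the same words, in the Phase 3 aims and in Statistical Analysis. Progression without modification requires all of:

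- more than 70% of intervention participants rating the resources *very acceptable*, with the denominator and the handling of non-raters stated (at least 29 if all 40 are counted);
- consent above 70%, with its denominator;
- 6-month follow-up above 80%, with its denominator (at least 49 if all 60 are counted).

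These are the protocol's own thresholds from the aims. In addition:

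- Say what the second value in Statistical Analysis refers to.
- State the expected value separately from the threshold.
- Make the 70% and the intervals agree: keep 70% with 53.5%-83.4% (n = 40) and 56.8%-81.2% (n = 60), or keep the printed intervals and state 75%.
- Quote the probability of meeting the acceptability criterion (at least 29/40): 7%, 44%, 72% and 91% at true rates of 60%, 70%, 75% and 80%.

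The cost is wording only, with no added participants or procedures. The downside is that the combined rule is somewhat harder to meet than acceptability alone.
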